### Outcome and statistical analyses

For all planned analyses baseline data will be presented with descriptive statistics; continuous variables as mean with standard deviation and categorical variables as frequency with percentages. A detailed overview of research questions and statistical analyses are described in the following section. All analyses will be performed using SPSS v 23 (IBM Corp. Armonk, NY) and STATA v 16 (Stata Corporation LP; College Station, TX, USA).

**Research question 1:** Which are the clinical predictors and biomarkers predictors of pain response to palliative RT for CIBP?

*Objective*: To obtain demographic, clinical data and biomarkers before start of RT and compare with RT response for pain in order to develop a classification system relevant for predicting RT response.

*Outcome*: Primary endpoint is response to RT defined as at pain reduction of worst pain score of two or more at the treated site on the 11-point NRS together with no increase in analgesic intake, or a reduction in opioid intake of at least 25% from baseline without an increase in worst pain score at the treated site [18]. Patients with two or more radiation locations are defined as responders if they respond in one of the included sites. Patients who die before the first assessment (3 weeks after RT), will be defined as non-responders because these patients have not benefited from RT. Patients with missing data on outcome measurements including pain intensity at the treated site or the use of analgesic medications will not be included in the analyses.

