### Expected limitations

As for all studies on palliative cancer patients we expect the number of drop-outs and missing data to be relatively high. A reason for drop-out before evaluation of treatment response may be that the patients are too sick or because of high symptom burden. These patients cannot be included in the predictive analyses as they are not missing at random and may bias the results. The patient inclusion is also for practical reasons not consecutive and the sample size of 600 do not allow for a validation sample analyses. Also, in order to assess the adverse effects from RT, a day-to-day evaluation of symptoms after RT would have given important information but were not performed in order to simplify data collection for the patient population.

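### The primary endpoint drops every patient missing pain or analgesic data, although an observed rise in opioid intake, or in worst pain at every treated site, already establishes non-response

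*Protocol article*

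**What the plan says.** Protocol article, Outcome and statistical analyses, Research question 1 (Outcome), gives two routes to response. The first is "pain reduction of worst pain score of two or more at the treated site on the 11-point NRS together with no increase in analgesic intake". The second is "a reduction in opioid intake of at least 25% from baseline without an increase in worst pain score at the treated site". For several sites, "Patients with two or more radiation locations are defined as responders if they respond in one of the included sites".

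Incomplete follow-up is settled in two sentences. For early deaths, "Patients who die before the first assessment (3 weeks after RT), will be defined as non-responders". For everyone else, "Patients with missing data on outcome measurements including pain intensity at the treated site or the use of analgesic medications will not be included".

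Under Expected limitations the article foresees relatively high missingness and adds: "A reason for drop-out before evaluation of treatment response may be that the patients are too sick or because of high symptom burden". It then justifies exclusion: "These patients cannot be included in the predictive analyses as they are not missing at random and may bias the results".

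**The concern.** The exclusion sentence joins pain and analgesic use with an 'or', so one missing component is enough to remove a patient. Yet each route places a condition on both components, and an unfavourable value of one can close both routes. Such a patient's outcome is known, and it is non-response.

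The plan is also uneven. It keeps early deaths as non-responders on the ground that they did not benefit, but removes survivors whose non-response its own definition proves. Removing patients because they are not missing at random does not remove the resulting bias.

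Partly observed outcomes are plausible. Pain is self-reported (Clinical variables), and Table 1 lists medication use and pain registrations as separate items at every visit.

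At stake is the smaller outcome group. With about 60% expected to respond, non-responders limit a model with up to 29 clinical variables, and that model is to become a score for the likelihood of response.

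**Working it through.** **1. What one component can settle.** The plan gives no figure for this rule, so the first check is logical. I ran every combination of pain change, opioid change and non-opioid change through the two routes for one treated site at one assessment.

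| Observed | Missing | Possible outcome |
|---|---|---|
| Worst pain rose | Analgesics | Non-response only |
| Worst pain unchanged, or fell by any amount | Analgesics | Either* |
| Opioid intake rose | Pain | Non-response only |
| Non-opioid rose, opioid not down by 25% or more | Pain | Non-response only |
| Non-opioid rose, opioid down by 25% or more | Pain | Either |
| No analgesic rise | Pain | Either |

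*With no opioid at baseline the second route is closed, so any pain change short of a 2-point fall also means non-response.

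No row gives response only.

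**2. Several sites.** One responding site suffices. An opioid rise closes both routes at all sites. A pain rise is decisive only if it occurs at every treated site. Conversely, a patient who responds at one site with another site's pain missing is a known responder, whom a literal reading of the rule could drop.

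**3. How many known non-responses are lost.** From the document: 600 patients and about 60% response. Assumed: a share m of 5-15% with exactly one component missing, and a share r of 25-75% of the non-responders among them showing a rise in the observed component.

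Known non-responders dropped = 600 × m × 0.4 × r
- m = 5%, r = 25%: 3
- m = 10%, r = 50%: 12
- m = 15%, r = 75%: 27

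A simulation agrees in order of size. It assumed pain change with mean -2.2 and SD 2.6, correlation 0.4 with analgesic change, and 60% or 80% on opioids. Each component was missing at random in 5% of 600 × 0.8 = 480 patients. Dropped: 480 × (1 − 0.95²) ≈ 47, of whom about 8 (17%) were certain non-responders. In a similar simulation under random missingness the complete-case response rate equalled the full-data rate (54.1% in both).

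**4. Missingness linked to outcome.** Let a be the share of patients whose opioid intake rose (all non-responders), and let pain be missing in a share q of them and in 5% of the others. Then

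complete-case rate = 0.60 × 0.95 / [(1 − a) × 0.95 + a × (1 − q)]

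| a | q | Complete-case rate | Excess over 60% | Certain non-responders lost per 480 (480 × a × q) |
|---|---|---|---|---|
| 15% | 20% | 0.57/0.9275 = 61.5% | 1.5 points | 14 |
| 15% | 30% | 0.57/0.9125 = 62.5% | 2.5 points | 22 |
| 20% | 20% | 0.57/0.92 = 62.0% | 2.0 points | 19 |
| 20% | 30% | 0.57/0.90 = 63.3% | 3.3 points | 29 |

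Simulations with the pain distribution of step 3, and the same assumed missing rates, gave 1.5 to 3.0 points and 10 to 30 certain non-responders lost. In one of them 56.1% became 57.6-58.7%. For scale, 480 × 0.4 = 192 non-responders, or 192/29 = 6.6 per clinical variable.

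**5. Predictor coefficients.** One standard-normal predictor was added under similar assumptions (70% on opioids, analgesic rise in about 20%). The complete-case log-odds slope, divided by the full-data slope, was:
- 1.04-1.07 when the predictor acted on pain only;
- 0.97-0.99 when it acted on both components;
- 0.80-0.89 when it acted on analgesic change only.

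**6. Why classifying the certain cases alone is not enough.** Under random missingness with m = 10% and r = 50%, adding back only the 12 known non-responders gives (540 × 0.60)/(540 + 12) = 58.7%, below the true 60%. At m = 15%, r = 75% it is 306/537 = 57.0%.

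**The case against.** The strongest reply is that this is a narrow efficiency point, partly disclosed already. Expected limitations admits high, non-random missingness, and early deaths are already counted as non-responders. Research question 1 seeks predictors, not a prevalence, so a shift of 1.5 to 3 points falls mainly on the intercept. The document gives no rate of one-component missingness, and does not say that a medication record exists when a patient is too ill to report pain. Multiple imputation ordinarily assumes missing at random, which the plan itself doubts.

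Much of this stands. The effect is modest and its size is assumed. It also limits what a reader might infer:

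- That the rule in itself biases the analysis. It does not: with components missing completely at random, only precision is lost.
- That predictor effects are generally attenuated. Step 5 shows movement in either direction, depending on the predictor.
- That known responders are never dropped. The rule for several sites allows it, and the share of such patients is not stated.

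The reply does not defend the rule. Disclosing non-random missingness does not justify discarding outcomes that are already determined. The intercept matters because the model is to yield a score for likelihood of response. The doubt about imputation calls for sensitivity analyses and does not favour complete cases, which carry their own assumption.

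**Conclusion.** The point holds as a modest one that should be fixed. Under the plan's own definition, a rise in opioid intake, or in worst pain at every treated site, establishes non-response; the exclusion rule discards such patients and the observed half of every other partly observed outcome. The logic rests only on the stated definition, applied at one assessment. If several visits counted towards response, a rise at one visit would settle only that visit.

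The consequence depends on the missing-data mechanism. Under completely random missingness it is lost precision. Under the outcome-related missingness that Expected limitations anticipates, the response rate and the score's intercept are too high, by about 1.5 to 3 points at assumed rates of 20-30% versus 5%. Coefficients may shift either way. The point concerns partly observed outcomes, not patients with no outcome data.

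**What to change.** For patients with partly observed outcomes at the response assessment, replace the exclusion sentence by wording such as:

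> A patient with one component missing is a non-responder if opioid intake increased, or if worst pain increased at every treated site. A patient who meets the response definition at one site with complete data is a responder even if another site is missing. For the remaining patients with one component missing, the missing component is multiply imputed from the observed component, baseline values and adjacent visits, with complete-case and not-missing-at-random sensitivity analyses.

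Both steps belong together, for the reason in step 6. The other determined cases in step 1 (a non-opioid rise without a 25% opioid fall; no baseline opioid and less than a 2-point pain fall) resolve correctly if the response definition is applied after imputation and a patient without baseline opioid cannot be imputed an opioid reduction.

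The cost is one changed paragraph in the endpoint derivation, somewhat more analysis work, and a missing-at-random assumption for the undetermined cases, which the sensitivity analyses probe. No new data are needed.

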### Power consideration

The sample size is based upon the primary outcome; response to RT for pain [18]. The analyses plan includes up to 29 independent clinical variables (see previous sections for variables marked with an asterisk.) A full statistical estimate of sample size requires knowledge of the variance-covariance matrix, which was not available at the planning stage of this study. Therefore, the widely-used rule of thumb of 10 x number of variables was adopted. This reasoning resulted in a sample size of 290. Based upon experience, interactions will arise which increases the needed number of patients, and up to 20% of patients were expected to be lost to follow-up. To account for this, the number of needed patients was set to 600. The original protocol plan was to include a validation sample of 1/3 of patients resulting in a total number of 1000 included patients. But because of slow recruitment, we had to close the study after 600 recruited patients, and the analyses will therefore be performed without the planned validation sample.

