*Statistical method*: Clinical variables (see previous chapter) and CRP will be included in a multivariate logistic regression model to predict potential factors for response to RT. The model will be adjusted by study centre. Regression diagnostics will be performed for all analyses adding interactions terms if necessary. Significant variables from the multivariable model will be presented as a response-score to determine the likelihood of response to RT. Second, we will perform analyses on inflammatory biomarkers and bone biomarkers correlated with response to RT. Only inflammatory biomarkers and bone biomarkers with levels of serum concentrations above the detection threshold and which have a variability between measurements will be analysed with a multivariate logistic regression model with response to RT as the dependant variable. Finally, an integrated regression model with response to RT including both the significant clinical variables and significant biological biomarkers will be conducted if appropriate based on results from the previous analyses.

**Research question 2:** Which inflammatory biomarkers are associated with change in pain intensity in patients with CIBP?

*Objective*: To investigate the correlation between pain intensity and inflammation. Patients included in the PRAIS study all have CIBP and will receive a standardized intervention expected to give pain relief in about 60% of the patients. This study can explore if there is a longitudinal relationship between changes in pain intensity and the detected level of inflammatory biomarkers.

*Outcome*: Serum concentrations of inflammatory biomarkers as described above associated with changes in pain intensity as measured by average pain intensity and worst pain intensity last 24 h (NRS 0–11) for a maximum of 1 year follow-up.

*Statistical method*: Longitudinal data analysis with repeated measurements using a liner mixed effect model or generalized estimating equation (GEE).

**Research question 3:** Which inflammatory substances are associated with cancer cachexia?

*Objective*: To gain insight into the role of inflammation in cancer cachexia.

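### Interaction terms may be chosen from the same data that build the primary response score, and no validation sample remains to show the resulting overfitting

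*Protocol article*

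**What the plan says.** The protocol article, Outcome and statistical analyses, Research question 1, sets out the primary model: "Clinical variables (see previous chapter) and CRP will be included in a multivariate logistic regression model", and "The model will be adjusted by study centre". It continues: "Regression diagnostics will be performed for all analyses adding interactions terms if necessary". The next step is the product of the primary analysis: "Significant variables from the multivariable model will be presented as a response-score". Interactions that enter the model can therefore reach the score.

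The section Power consideration says "The analyses plan includes up to 29 independent clinical variables" and that "the widely-used rule of thumb of 10 x number of variables was adopted". It treats interactions as likely: "Based upon experience, interactions will arise which increases the needed number of patients". It also reports that recruitment closed at 600 patients instead of 1000, so that "the analyses will therefore be performed without the planned validation sample". The section Expected limitations repeats that no validation sample is possible.

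**The concern.** A term that is added because the development data seem to call for it has been fitted partly to noise. Its apparent contribution is too large, and the same patients cannot show this. The article keeps the data-dependent step but has lost the separate sample that would have exposed its effect.

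The Background and Discussion sections say that prediction should help identify patients who are unlikely to benefit from radiation therapy. A score whose predicted probabilities are too extreme would classify patients with more certainty than the data justify, and its reported accuracy would not reveal this.

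**Working it through.** **Inputs from the protocol article**
- Candidate clinical variables: up to 29 (Power consideration). The section Clinical variables marks 24 with an asterisk. CRP adds one. The number of centres is not given.
- Planning rule: 10 patients per variable. Loss to follow-up: up to 20%. Final size: 600.
- Expected response: about 60% (Research question 2).
- Significance level: not stated; 0.05 is assumed.

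**The plan's own figure.** 10 × 29 = 290, as stated. Loss to follow-up alone gives 290 / 0.80 = 363. The rest of the increase to 600 is an allowance for interactions that has no number. It can be read backwards: 600 × 0.80 = 480 evaluable, 480 / 10 = 48 terms, and 48 − 29 = 19 terms at most beyond the clinical variables.

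With 60% response, the 480 patients include 480 × 0.40 = 192 non-responders. That is 192 / 29 = 6.6 per term without interactions and 192 / 48 = 4.0 with 19 of them.

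**How many pairs could be tried**
- 24 marked variables plus CRP: 25 × 24 / 2 = 300 pairs, and 300 × 0.05 = 15 expected to reach p<0.05 by chance.
- 29 variables plus CRP: 30 × 29 / 2 = 435 pairs, and 435 × 0.05 = about 22.

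**Effect on the score, no true interaction.** The simulations used 480 patients and 25 predictors, and checked each model in new patients. Effect sizes and selection rules are assumptions. Two separate sets were run, so each row should be compared with the main-effects row of its own set.

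| Set | Rule for interactions | AUC, new patients | Loss | Calibration slope |
|---|---|---|---|---|
| A | None (main effects) | 0.702 | – | 0.71 |
| A | Three named in advance | 0.700 | 0.002 | 0.68 |
| A | Single best pair in the data | 0.693 | 0.009 | 0.62 |
| A | Best three pairs in the data | 0.682 | 0.020 | 0.52 |
| A | Every pair with p<0.05 | 0.659 | 0.043 | 0.34 |
| B | None (main effects) | 0.712 | – | 0.71 |
| B | p<0.05 screen, only after a failed Hosmer-Lemeshow test | 0.710 | 0.002 | 0.69 |
| B | p<0.05 screen, only after a failed link test | 0.710 | 0.002 | 0.70 |
| B | Every pair with p<0.05 | 0.668 | 0.044 | 0.35 |

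In set B the apparent AUC rose from 0.771 with main effects to 0.847 under the full screen. The gap between apparent and new-patient AUC thus grew from 0.771 − 0.712 = 0.06 to 0.847 − 0.668 = 0.18. A further run with 25 predictors put the loss under the full screen at 0.69 − 0.64 = 0.05, with slope 0.30.

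**The score as planned (significant variables only).** This was checked with 29 predictors and forward selection at p<0.05. With no interactions the AUC was 0.76 apparent and 0.73 in new patients, slope 0.84. With ten data-chosen terms it was 0.83 and 0.68, slope 0.38. Reducing the model to significant variables does not remove the problem. In the full 29-predictor model, filling all 19 places lowered new-patient AUC from 0.72 to 0.65, with slope 0.21.

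**When a true interaction exists (29 predictors).** With a strong interaction (coefficient 0.6) and a strict rule (p<0.001, at most three terms), new-patient AUC rose from 0.690 to 0.719. Three named terms that included the true one gave 0.724. A loose rule (p<0.05, up to ten terms) gave 0.683.

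**The case against.** The strongest reply is that this is one conventional model-checking sentence. Terms are added only when diagnostics show a need, which is not a search through all 300 pairs. A reader might infer from the sentence that such a screen is planned. The text does not say so, and gives no threshold of 0.05 or any other. If terms follow only a failed global test, such a test fails seldom when no interaction exists (6.7% of data sets for Hosmer-Lemeshow, 4.2% for the link test), and the average harm is close to nil. This stands, and it sets the lower end of the range.

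A reader might also infer that the rule must make the score worse. That is not supported either, because a strong true interaction found under a strict rule improved it.

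A third reply is that a condensed article may leave a list of interactions, a criterion and a maximum to the full protocol or SAP. This is fair, and their absence is not the point made here. The point is the rule that the article does state: need is judged on the development data, and the result enters the score. A closed list elsewhere would replace that rule.

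Finally, the sample was enlarged partly for interactions, the lack of validation is disclosed, and the main-effects model already overfits (slope about 0.7). All three are true. The enlargement has no number attached, disclosure does not reduce optimism, and data-chosen terms add to the overfitting already present.

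**Conclusion.** The concern holds as a cheap improvement. The stated rule lets interactions be selected from the data that build the primary score, the article expects this to happen, and no separate sample remains to show its effect. Apparent accuracy is inflated, and performance in new patients can fall.

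The size is uncertain because the selection rule is not fixed. With 480 evaluable patients, 25 predictors, assumed effects and no true interaction, the loss is:
- about zero if terms are added only after a failed global diagnostic;
- about 0.01 to 0.02 AUC, with slope about 0.6 to 0.5, for one to three data-picked pairs;
- about 0.04 to 0.05 AUC, with slope about 0.3, if every pair with p<0.05 is added. This is the worst case of the 25-predictor runs and should not be quoted as the expected effect.

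The direction is well supported when no interaction exists. It can reverse when a strong one exists and the rule is strict.

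**What to change.** Replace the sentence on interactions under Research question 1 with a rule to this effect:
- The primary model and the score contain main effects plus a short closed list of interactions named before the outcome data are analysed, or none. The listed interactions are tested together in one global test.
- Regression diagnostics serve to check functional form and influence.
- Any interaction found later is reported as exploratory and kept out of the score.
- Apparent performance is reported with a bootstrap optimism correction that repeats every selection step, including the reduction to significant variables.

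The bootstrap supplements the closed list and does not replace it. In a small check (6 data sets, 40 resamples each, up to ten data-chosen terms) it brought an apparent AUC of 0.86 down to 0.74, against 0.68 in new patients.

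The cost is a short change of text and some computing, with no new data. Naming three interactions cost almost nothing in the simulations (0.702 to 0.700). The downside is that a true but unanticipated interaction would be reported only as exploratory.

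### The response score is built from the significant variables of one model, and no internal validation replaces the dropped validation sample; bootstrap validation would need no extra patients

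*Protocol article*

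**What the plan says.** All statements are in the protocol article.

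- **Candidates.** Power consideration: "The analyses plan includes up to 29 independent clinical variables". The asterisks under Clinical variables mark 24 items. Outcome and statistical analyses, research question 1: "Clinical variables (see previous chapter) and CRP will be included in a multivariate logistic regression model". The model is adjusted for study centre.
- **Interactions.** Same section: "Regression diagnostics will be performed for all analyses adding interactions terms if necessary".
- **Score.** Same section: "Significant variables from the multivariable model will be presented as a response-score to determine the likelihood of response to RT". No significance level is given.
- **Biomarkers.** Inflammatory and bone markers are analysed in a second step. A further regression, "including both the significant clinical variables and significant biological biomarkers will be conducted if appropriate based on results from the previous analyses", may follow. It is conditional and is not described as the score.
- **Validation.** Power consideration reports that one third of 1000 patients was to serve for validation, that recruitment was slow, and that "the analyses will therefore be performed without the planned validation sample". Expected limitations adds that "the sample size of 600 do not allow for a validation sample analyses".
- **Purpose.** The objective of research question 1 is a classification system for predicting response. The Discussion foresees such data being used in routine care to choose patients for radiotherapy.

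**The concern.** When one data set chooses the score items, sets their weights and supplies the only assessment, three things follow:

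- Variables that pass a significance threshold do so partly because their estimates are too large in this sample. Their weights are therefore exaggerated, and predicted likelihoods lie too close to 0 and 1.
- With about 30 candidates, some items will pass by chance.
- Any accuracy computed on the same patients is optimistic.

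A validation sample would have exposed this. The reason given for dropping it, sample size, applies to a held-out sample. It does not apply to resampling, which uses every patient for both development and assessment.

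The stake is the main product of the study. A score meant to help identify patients unlikely to benefit from radiotherapy should not be more confident than its data support.

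**Working it through.** **1. The plan's own figure.** Power consideration applies 10 patients per variable: 10 × 29 = 290, which reproduces. Allowing for 20% loss gives 290 / 0.8 = 362.5, so 363. The rest of the step to 600 is an allowance for interactions that is not quantified, so 600 can be neither derived nor called wrong.

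**2. Information per candidate.** For a binary outcome, the smaller outcome class limits the model. Inputs are 600 patients, up to 20% loss and about 60% response, all from the article.

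- Evaluable: 600 × 0.8 = 480.
- Non-responders: 480 × 0.4 = 192.
- Per candidate: 192 / 29 = 6.6. With CRP as a 30th candidate it is 192 / 30 = 6.4, and with the 24 asterisked items 192 / 24 = 8.0.
- Range with 30 candidates at 480 patients: 8.0 (50% response) to 5.6 (65% response).
- With no loss: 600 × 0.4 = 240, and 240 / 29 = 8.3.

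**3. Chance selection.** Assume a 5% level and independent tests. If all 30 candidates were noise, 30 × 0.05 = 1.5 would be expected to pass, and the chance of at least one is 1 − 0.95^30 = 0.79.

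**4. Simulation of the stated rule.** Fit the full logistic model, keep variables with p < 0.05, refit, and compare the AUC in the development data with the AUC in a large set of new patients. The effect sizes are assumptions, since the article gives none. Set-up A has 30 standardised predictors with pairwise correlation 0.2 and either 5 real predictors or none. Set-up B has 29 independent predictors, 6 of them real. Response is about 60% in both.

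| Set-up | n | Real effects per SD | Apparent AUC | AUC in new patients | Calibration slope |
|---|---|---|---|---|---|
| A | 480 | none | 0.580 | 0.500 | about 0 |
| A | 480 | 5, log-OR 0.2 | 0.667 | 0.613 | 0.65 |
| A | 480 | 5, log-OR 0.3 | 0.733 | 0.695 | 0.80 |
| B | 480 | 6, OR 1.28 | 0.68 | 0.62 | 0.65 |
| B | 480 | 6, OR 1.5 | 0.756 | 0.723 | 0.83 |
| A | 600 | 5, log-OR 0.2 | 0.664 | 0.615 | 0.68 |
| A | 600 | 5, log-OR 0.3 | 0.732 | 0.703 | 0.84 |
| B | 600 | 6, OR 1.5 | 0.750 | 0.726 | 0.88 |

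The row without real effects averages over data sets in which at least one variable was selected. At 480 patients the excess in AUC is 0.756 − 0.723 = 0.033 at the low end and 0.68 − 0.62 = 0.06 at the high end when some predictors are real, and 0.080 when none is. In set-up A at 480 patients, at least one noise variable entered the score in 73% to 83% of data sets. The simulations contain no centre effects or interactions and no multi-category predictors, all of which would tend to add optimism.

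**5. Does the bootstrap work at this size?** Set-up A, 480 patients, selection repeated in each resample (30 data sets, 60 resamples each):

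| Real effects | Apparent | Bootstrap-corrected | In new patients |
|---|---|---|---|
| none | 0.589 | 0.517 | 0.499 |
| 5, log-OR 0.2 | 0.666 | 0.607 | 0.611 |
| 5, log-OR 0.3 | 0.728 | 0.679 | 0.689 |

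The correction removes most of the optimism without any additional patient.

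**The case against.** The strongest reply has four parts.

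*An article condenses a fuller plan.* Internal validation, shrinkage and performance measures may be set out elsewhere. That is fair for the details. But the article itself fixes the rule that turns significance into score items, and it says that the analyses go ahead without the planned validation. A plan that followed this text would give an unvalidated score.

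*The limitation is disclosed, and the language is modest.* Both are true, and the authors deserve credit for stating it twice. The abstract speaks of potential predictors. Disclosure does not correct the weights, however, and the stated purpose remains a tool for choosing patients.

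*The size rests on assumed effects.* This stands. With stronger predictors the optimism falls to about 0.03 (slope 0.83) at 480 patients and to 0.750 − 0.726 = 0.024 (slope 0.88) at 600. The case with no real predictor is a bound rather than an expectation, since the Background cites two large studies in which cancer type and performance status predicted response.

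*Several stronger readings go too far.*

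- A reader might infer that the article rules out all validation. It rules out only a validation sample and is silent on resampling.
- A reader might infer that significant biomarkers are added to the score. The score comes from the model of clinical variables and CRP. The integrated model is separate and conditional, and it already adjusts each marker for the significant clinical variables.
- A reader might count the 33 markers in Table 2 and conclude that an 82% chance of a false positive is built in (1 − 0.95^33). Only detectable, variable markers are analysed, so 33 is a ceiling. With 20 markers the chance would be 1 − 0.95^20 = 64%. The Discussion also calls the inflammation work exploratory.

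**Conclusion.** The point holds for the clinical response score of research question 1. It is built from variables chosen for significance in a single data set, and nothing named in the article replaces the dropped validation sample.

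The expected overstatement at 480 evaluable patients is about 0.03 to 0.06 in AUC when some predictors are real, and about 0.08 when none is. Predictions are too extreme, with a slope of about 0.65 for weak effects and 0.80 to 0.83 for stronger ones. It is usual for at least one noise item to enter.

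These figures assume a 5% selection level, 20% loss, 60% response and the effect sizes shown. The article names neither the level nor an accuracy measure. The overstatement therefore concerns any discrimination or predicted likelihood that would be derived from the score, and it should not be read as a claim about a result the article promises to report. The case for change rests on a stated rule with a known bias and a remedy that costs little.

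**What to change.** 1. Derive the score from a prespecified full or penalised logistic model, or keep the stated selection and declare its significance level.
2. In either case, repeat every data-driven step (variable selection and any interactions) in at least 500 bootstrap samples.
3. Report the optimism-corrected AUC and calibration slope beside the apparent values, and shrink the published weights accordingly. A penalised fit already does part of this.
4. If the integrated biomarker model is run, include the marker screening in the same bootstrap and report the markers as exploratory. False discovery rate control, a likelihood ratio test of the marker block against the clinical model, and validation by centre are optional additions.
5. In Expected limitations, say that a held-out sample was not possible and that internal validation by bootstrap was used instead.

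The cost is programming time and a somewhat lower reported accuracy, with no extra patients or data. The bootstrap estimates performance in patients like those enrolled. It does not replace testing the score in new patients, and the report should say so.
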